# Impact Assessment of the Allergy Fact Checker, a Clinical Decision Support Tool for Noninvasive Beta-Lactam Antibiotic Allergy Label Delabeling: Protocol for a Multicenter Crossover Cluster-Controlled Study

**DOI:** 10.2196/86056

**Published:** 2026-03-27

**Keywords:** antibiotic allergy label, antimicrobial stewardship, beta-lactams, clinical decision support, delabeling, drug allergy, electronic patient records, noninvasive delabeling, medical records, penicillin

## Abstract

**Background:**

Beta-lactam allergy labels (BLALs), especially penicillin allergy labels, are frequently recorded in hospitalized patients and are associated with increased use of broad-spectrum and second-line antibiotics. Most BLALs are incorrect, but current allergy workups require invasive testing and specialized resources. We recently developed a strictly noninvasive, electronic patient record–embedded clinical decision support tool, the Allergy Fact Checker (AFC), which proactively identifies potentially incorrect BLALs by detecting uneventful re-exposures to the culprit or other beta-lactams since introduction of the BLAL.

**Objective:**

This study aims to evaluate the clinical, antimicrobial, and economic impact of the AFC in hospitalized adults with BLALs compared to the standard of care (no AFC).

**Methods:**

We are conducting a multicenter, open-label, crossover cluster-controlled study in 9 hospitals in Flanders, Belgium. All hospitalized adults with a BLAL are eligible, excluding patients in palliative care, discharged within 24 hours, or previously enrolled. Each hospital will alternate between intervention (use of the AFC) and control (standard practice) phases, separated by washout periods. The primary endpoint is cumulative guideline-concordant prescribing of first-line and/or narrow-spectrum beta-lactams following local antibiotic treatment guidelines, across predefined care windows up to day 100, expressed as a weighted per-patient proportion. Secondary endpoints include delabeling or refinement rate, beta-lactam tolerance, antibiotic switching, hospital length of stay, in-hospital and 3-month mortality, intensive care unit admission, readmission, multidrug-resistant organism colonization or infection, and costs. Based on prior data, we calculated that a total of 3285 participants are required to achieve 80% power to detect superiority of the intervention (4.6% vs 9.9% appropriate prescribing). Recruitment started in March 2025 and is ongoing.

**Results:**

The primary outcome will be analyzed using hierarchical mixed-effect models accounting for hospital-level clustering and period effects. Data collection will continue until 200 days after the last patient is discharged. This trial is expected to conclude in 2026. Ethical approval was obtained from the institutional review board in November 2024. Recruitment started in March 2025 and is ongoing. As of manuscript submission, more than 3000 participants have been enrolled across the participating hospitals. According to the prespecified protocol, an interim assessment of nuisance parameters will be performed in the following month to evaluate the initial design assumptions. Data collection is expected to continue until the end of 2026. The main study results are anticipated to be reported in 2027.

**Conclusions:**

This is the first multicenter European study evaluating a strictly noninvasive BLAL delabeling approach. If successful, this AFC tool could improve antimicrobial stewardship, reduce costs, and provide a scalable model for centralized allergy label management.

## Introduction

Drug allergy labels are an important tool to improve patient safety. They aim to reduce potential harmful re-exposure by alerting health care providers (HCP) of a prior allergic reaction. However, labeling is often insufficiently accurate, and an incorrect label may even cause harm through unnecessarily restraining patients from a first-choice treatment. Antibiotic allergy labels are the most frequently reported drug allergy labels [1]. Especially the prevalence of beta-lactams, which are first-choice treatments in most bacterial infections because of their spectrum, safety, low cost, and availability, is high. In US studies, the prevalence of beta-lactam allergy labels (BLALs) reported in electronic patient records (EPR) ranges between 9% and 16% [2-6], whereas European studies report a significantly lower prevalence of 1% to 5% [7-10]. In our center, covering over 1 million patients over an 8-year period, the observed BLAL prevalence was 2%, with rates varying from 1% in outpatient settings to 6% among hospitalized patients [11].

Most BLALs are incorrect. Upon a complete drug allergy workup, which includes a thorough clinical history, invasive skin and drug provocation testing, the majority of BLAL, especially penicillin, can be invalidated ranging from 95%‐99% of patients with a penicillin allergy label in United States and Australian studies [1-9], to 77%‐91% in European Union (EU) studies [10,11].

The impact of BLAL, irrespective of the correctness of the label, has been studied primarily in non-EU settings and mostly for penicillin. Penicillin allergy labels were associated with increased use of second-line and broad-spectrum antibiotics, a delay in time-to-first-dose upon admission [1,6,12], and increased odds for infection with antibiotic-resistant organisms [13-15]. Moreover, an increased length of hospital stay (LOS), mortality, intensive care unit (ICU) admission rate [5,16,17], and a higher economic cost [18-20] were found. Recent work from our group suggested that BLALs have limited impact on individual clinical outcomes (ie, no increased mortality, ICU admission rate, or increased LOS), although their effect on antibiotic use remains in line with findings from non-EU studies [21].

These concerns led to the emergence of invasive delabeling protocols for penicillin allergy labels in the United States and Australia [22,23]. Current approaches use risk stratification based on clinical history and direct challenges (ie, in-hospital, but without prior skin tests) with penicillins or alternative beta-lactams in identified low-risk patients [24,25]. The efforts demonstrate to be cost-effective [22] and impact antibiotic use, shifting more to first-line beta-lactams and narrow-spectrum penicillins [26]. However, a relevant fraction of readministrations was accompanied by a repeat hypersensitivity reaction (3.8%), of which a minority (<1%) were severe [26]. This illustrates the delicate balance between indirect harm through incorrect BLAL and repeat iatrogenicity through invasive delabeling protocols themselves.

An often forgotten step in the delabeling process that encompasses the lowest risk for repeat iatrogeny is noninvasive delabeling. Here, without skin or drug provocation testing, but solely by using patient questionnaires and information from tolerated antibiotic exposures, discordances in the EPR are exploited to the advantage of the patient [9,27-29]. Our group prospectively evaluated in an EU context a noninvasive delabeling protocol in adult internal medicine inpatients with a BLAL [30], combining (1) an allergy-oriented clinical history, (2) an EPR search to identify incorrect BLAL and/or uneventful re-exposures to beta-lactams, and (3) a systematic primary care physician and community pharmacist contact. Using this approach, 38% of BLALs could be delabeled, and another 27% could be refined, largely driven by EPR findings. In the next step, we optimized the EPR search by developing a semiautomated clinical decision support (CDS) tool, designed to identify those patients with documented re-exposure without allergic reaction. A proof-of-concept study, limited to penicillin allergy labels, demonstrated the feasibility and efficacy of this novel CDS tool, identifying nearly 10% of alleged penicillin-allergic patients and showing approximately sevenfold higher odds of delabeling after its introduction [31]. Importantly, the impact on prescription behavior and major clinical outcome parameters is unknown and would be the basis for broad roll-out. Therefore, we propose to perform the first multicenter study on noninvasive BLAL delabeling, using an EPR-embedded, semiautomatic, intelligent “Allergy Fact Checker (AFC)” CDS tool.

## Methods

### Aim

This study aims to evaluate the clinical and economic benefits of a noninvasive CDS tool, critically assessing BLALs the AFC, while following local antibiotic treatment guidelines. Specifically, we will assess its impact on antibiotic use, as well as clinical, antimicrobial, and economic end points in hospitalized adults with BLAL. We hypothesize that a relevant fraction of BLAL can be rationalized by the AFC, thereby improving antibiotic use and costs without impacting morbidity or mortality.

### Design

A multicenter, open-label, crossover cluster-controlled trial will be conducted to compare the use of our AFC on BLAL (intervention, I) and subsequent antibiotic prescription with current practice (control, C, ie, no AFC). All hospitalized adults with one or more BLAL will be included, except those previously enrolled in this study, discharged within 24 hours, or in palliative care. The primary endpoint is cumulative guideline-concordant prescribing of first-line and/or narrow-spectrum beta-lactams (based on the IGGI [Infectiologiegids/Guide d’Infectiologie] guidelines of the Belgian Society for Infectiology and Clinical Microbiology) across predefined care windows up to day 100, expressed as a weighted per-patient proportion. Within each predefined assessment window, prescribing is scored in an any or ever binary manner, and a cumulative weighted score per patient is calculated across applicable windows. Secondary endpoints include proportion of delabeled and refined BLALs; beta-lactam antibiotic tolerance; need to switch antibiotics; in-hospital and 3-month posthospitalization mortality; LOS; 3-month readmission rate; ICU admission rate; colonization and/or infection with methicillin-resistant *Staphylococcus aureus*, vancomycin-resistant *Enterococcus*, *Clostridium difficile* (*C. diff*); antibiotic and hospitalization cost, time, and resources needed for the AFC; and physician appraisal of the approach.

We chose a mono-faceted intervention without an awareness campaign or educational component (eg, e-learning for physicians on BLAL labeling and delabeling) to evaluate the impact of the AFC itself, enhancing its extrapolation afterward. To correct for interhospital variability, we choose a clustered crossover design. The crossover design also accounts for seasonal variability, for example, in overall antibiotic use.

Allocation is performed on the hospital level (participating sites) before the start of this study to prevent contamination of effect between the intervention and control phases (ie, so that physicians will not receive information through the AFC while having to use conventional means for different patients at the same time). The allocation is nonrandomized and operationally predefined based on the availability of a single trained research team responsible for on-site implementation across hospitals. Inclusion periods are sufficiently long and distributed over calendar time to account for seasonal variation. A crossover cluster-controlled design was used to reduce potential confounding related to temporal and organizational factors in clinical practice, such as variation in staffing and workload among treating physicians. Residual temporal and cluster-level confounding will be further addressed in the statistical analysis by including study period and hospital as model terms.

During separate intervention phases, hospital physicians will receive the intervention, that is, BLAL CDS. Each of the crossover periods will be 3 weeks long. However, a washout period of 3 weeks is also taken into account to allow the patient population to be sufficiently “new” before the cluster transitions to the next condition. We will use the sequences I-x-C-x, x-I-x-C, C-x-I-x, and x-C-x-I (where I=intervention, ie, use of the AFC, and C=control, ie, standard of care [SOC], no use of the AFC, and x=washout period), and each cluster will be allocated to one of these sequences (Figure 1). Information about the assigned sequence is available to all people and groups involved in the research (ie, unblinded, open study).

**Figure 1. F1:**
[figure not shown]
Schematic representation of this study’s design.

### Setting

Patients will be recruited in 9 participating centers across Flanders, that is, the University Hospitals of Leuven (UZ [Universitair Ziekenhuis] Leuven), and the general hospitals of Pelt (Noorderhart Mariaziekenhuis), Mol (Heilig Hartziekenhuis), Herentals (AZ [Algemeen Ziekenhuis (general hospital)] Herentals), Turnhout (AZ Turnhout), Izegem (Sint-Jozefskliniek), Halle (AZ Sint-Maria Halle), Tienen (RZ Heilig Hart Tienen), and Malle (AZ Voorkempen). The expected recruitment period, from First Patient In to Last Patient In, is 11 months, starting March 10, 2025. The total inclusion period from First Patient In to Last Patient Out is expected to take approximately 18 months. The total period of intervention plus follow-up for every single patient depends on the LOS, that is, until 200 days after discharge from the hospital, to collect the secondary end point parameters: in-hospital mortality, 3-month posthospitalization mortality, LOS, and 3-month readmission rate. Patients who are still in the hospital when the end of the recruitment period is reached (estimated February 2026, when the needed sample size was reached) will be excluded. For comparison, in a recent retrospective study in UZ Leuven, involving 21,999 patients with pneumonia, pyelonephritis, infections associated with heart, kidney, liver, or lung transplantation, appendectomy, coronary artery bypass grafting, and total knee or hip replacement, the average LOS in UZ Leuven for patients with BLAL was 21 days (SD 39) [21].

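### Enrolled patients still in hospital when recruitment closes are excluded, which truncates length of stay, a secondary endpoint, mainly in each hospital's last active phase

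*Protocol article*

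**What the plan says.** Under Methods, Setting, the protocol article states that "Patients who are still in the hospital when the end of the recruitment period is reached" will be excluded. It estimates that point as February 2026 and ties it to reaching the sample size. The same section gives a recruitment length: "The expected recruitment period, from First Patient In to Last Patient In, is 11 months". It allows about 18 months to the last patient out and follows each patient to 200 days after discharge.

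Other parts of the article bear on this rule:

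- **Exclusion Criteria** lists age under 18, previous enrolment, palliative care and expected discharge within 24 hours. The still-in-hospital rule is not there.
- **Abstract, Results:** "Data collection will continue until 200 days after the last patient is discharged".
- **Missing Data** censors survival-type outcomes at last known follow-up.
- **Follow-Up or Outcome Measurement** expects no loss to follow-up within participating hospitals, because outcomes are extracted from the electronic record.
- **Design:** "Each of the crossover periods will be 3 weeks long", with 3-week washouts, and "We will use the sequences I-x-C-x, x-I-x-C, C-x-I-x, and x-C-x-I". Also, "The allocation is nonrandomized and operationally predefined".
- **Statistical Analysis** uses fixed effects for phase and period with a random intercept for hospital. Secondary endpoints, LOS among them, get analogous models.
- **Results (end of article):** recruitment continues past March 2026 with three more hospitals. The exclusion is not withdrawn.

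**The concern.** Eligible patients are included during their admission, so the people removed by this rule are already in the study. In an intervention phase they may already have received the AFC review. What removes them is that their stay outlasts a date. That is selection on LOS, which the trial also compares between arms.

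The selection is uneven. Each hospital's last active phase is one arm only. Under x-I-x-C and x-C-x-I, that phase runs up to the end of the sequence. Under I-x-C-x and C-x-I-x, three weeks of washout give patients time to leave. So the share lost depends on sequence and, within a hospital, differs between arms. At stake is mainly the LOS comparison. The documents give no reason for the rule.

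**Working it through.** **The protocol's timeline.** 11 months + 200 days (about 6.6 months) = 17.6 months, which agrees with the stated 18 or so. Follow-up well past the cut-off is therefore already planned.

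**Share of one phase that is lost.** The protocol supplies LOS mean m = 21, SD = 39 days and the 3-week (21-day) phases and washouts. Assumptions: lognormal LOS, even entry over a phase, and a cut-off at the end of the sequence.

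- σ² = ln(1 + (39/21)²) = 1.493, σ = 1.222, μ = ln 21 − σ²/2 = 2.298, median 10.0 days.
- E[min(L, d)] = m·Φ((ln d − μ − σ²)/σ) + d·[1 − Φ((ln d − μ)/σ)].
- E[min(L, 21)] = 21 × 0.2706 + 21 × 0.2706 = 11.37.
- E[min(L, 42)] = 21 × 0.4826 + 42 × 0.1194 = 15.15.
- Active phase at the end: 11.37/21 = **54%** still in hospital.
- Phase followed by washout: (15.15 − 11.37)/21 = **18%**.

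With an assumed shorter stay (mean 8, SD 10; σ² = 0.941, median 5.0), the two expectations are 7.02 and 7.71. The shares are 7.02/21 = **33%** and (7.71 − 7.02)/21 = **3%**.

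A simulation that also drops stays under 24 hours gives 56% and 18% for the first case. Mean LOS among those kept falls from 21.6 to 5.9 days (active end) or 10.2 days (washout end).

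**Share of all patients.** Figure 1 is not available, so the number of cycles is an assumption. Active phases in a hospital start six weeks apart; 11 months is about 48 weeks, hence 48/6 = 8 phases if the sequences repeat. Percent lost, counting back from the last phase:

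| LOS | Sequence end | Loss by phase | Mean of 8 phases | Mean of 2 phases (one cycle) |
|---|---|---|---|---|
| 21 (39) | active | 54.1, 8.9, 3.3, 1.6, 0.9, 0.6, 0.4, 0.3 | 8.8% | 31.5% |
| 21 (39) | washout | 18.0, 5.2, 2.3, 1.2, 0.7, 0.5, 0.3, 0.2 | 3.5% | 11.6% |
| 8 (10) | active | 33.4, 0.8, 0.1, then about 0 | 4.3% | 17.1% |
| 8 (10) | washout | 3.3, 0.3, 0.1, then about 0 | 0.5% | 1.8% |

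**What this does to the LOS contrast with no true effect (simulation).**

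- Within one hospital (mean 21, SD 39), the arm of the last phase looks shorter by 7.2 days (active end) or 4.8 days (washout end) over the last pair of phases, and by 1.0 to 1.5 days over four cycles.
- Across nine hospitals with equal LOS, split 2/2/2/3 over the sequences, the unadjusted bias is 0.11 day (four cycles) to 0.56 day (one cycle). Adjusting for hospital and period brings it to zero.
- With one academic hospital (mean 21, SD 39) and eight regional ones (assumed mean 8, SD 11), an academic site of one or five times regional size, and one to four cycles, the hospital- and period-adjusted bias is 0.06 to 0.83 day in size. Its sign depends on the academic hospital's sequence.
- In that setting, an assumed 10% LOS reduction (true difference −0.97 to −1.14 days) is estimated anywhere from +0.19 to −1.40 days.

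**The case against.** Several counter-arguments stand:

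- The 54% and 18% describe one phase. A reader might infer that a large part of the trial is lost. With eight active phases the loss is single-digit, although fewer cycles would raise it.
- The 21-day mean comes from selected conditions, transplantation and bypass surgery among them, at the single academic site. Eight of the nine sites are regional, so the shorter-stay rows may be closer to the truth there.
- The final period contains both arms, through x-I-x-C and x-C-x-I, and period is in the model. A reader might infer that LOS will favour whichever condition came last across the trial. That holds within a hospital; it is not shown for the adjusted comparison.
- A reader might also infer bias in in-hospital mortality, ICU admission and the prescribing endpoint, or that the most antibiotic-exposed patients leave the primary analysis. The documents do not support this. Those excluded are alive at the cut-off and earlier deaths are kept, so the direction for mortality depends on how deaths and discharges are spread over the stay, which is not given. The prescribing score is a proportion of applicable windows with any/ever scoring and does not count courses. Long-stay patients from earlier phases almost all remain.
- Follow-up is anchored to discharge, and the 18-month total fits only if the last discharge falls near the end of recruitment. Deleting the rule therefore needs a censoring date to replace it.
- The February 2026 estimate has been overtaken, so the documents do not say which phase, in which hospitals, a new cut-off would hit.

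None of this gives a reason to keep the rule. The period term cancels the truncation only if it acts alike on both arms within a period. With nine hospitals, one of them academic, and nonrandom allocation, that cannot be assumed.

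**Conclusion.** The concern holds as a design flaw that directly affects LOS. The Setting rule removes enrolled patients on a realised secondary endpoint. It is missing from the exclusion criteria and inconsistent with both the planned follow-up and the censoring rule.

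The loss is concentrated in the last active phase: 54% against 18% by type of sequence ending with mean 21, SD 39, and 33% against 3% with the assumed shorter stay. Across eight assumed phases it is about 9% against 4%, or 4% against 0.5%. These figures are illustrative. They rest on a lognormal shape, even entry, a cut-off at the end of the sequence and an assumed number of cycles.

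The adjusted LOS bias could be nil or, under the assumed academic/regional gap, up to about 0.8 day either way. The documents settle neither its size nor its direction. Effects on in-hospital mortality, ICU admission and the primary endpoint remain possible, but indirect and unquantified.

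**What to change.** Delete the exclusion from Setting. Keep every enrolled eligible patient in the phase of enrolment. If recruitment needs a closing rule, apply it to the date of inclusion, which is known before the outcome. Follow patients to discharge and the planned time points, and name an administrative date at which LOS and time-to-event outcomes are censored for anyone still in hospital.

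Then reconcile Setting with the Abstract's data-collection statement, Exclusion Criteria, Missing Data and the extended recruitment reported in Results.

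The cost is small: a few sentences, with data that come from the electronic record anyway. Last patient out may move slightly, or a few stays will be censored. Recruitment was continuing and database lock was expected in late 2026 when the article was written, so on that timetable the change can be made before analysis.

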**Figure 2. F2:**
[figure not shown]
Schematic representation of the intervention vs standard of care. (1) Report baseline measurements eCRF; (2) automated search in the hospital EPR for re-exposure; (3) study team members receive AFC results on working list; (4) inclusion of patient in either standard of care or intervention (depending on scheme in Figure 1); (5) EPR check to identify BLAL for delabeling, refinement, or no action; (6) action is communicated to treating hospital physician (structured notes); (7) and (8) treating hospital physician can perform bedside verification and/or contact primary care HCP; (9) formal report of the results in the EPR; (10) letter to the primary care HCP; and (11) outcome parameters are followed up and scored in eCRF. AFC: Allergy Fact Checker; BLAL: beta-lactam allergy label; eCRF: electronic case report form; EPR: electronic patient record; GP: general practitioner; HCP: health care provider; REDCap: Research Electronic Data Capture; Vanderbilt University.

